5.1.2 Exclusion criteria

o Previous diagnosis of diabetes other than gestational diabetes (diabetes first diagnosed during a pregnancy) which has not persisted after pregnancy

o Previous treatment for IGT other than with routine dietary and health advice (persons previously given intensive diet or exercise treatment for IGT or other metabolic conditions such as hyperlipidemia will be excluded)

o Participation in a regular program of vigorous physical exercise

o A myocardial infarction or a by-pass operation less then 1 year ago o Hypersensitivity to diet or exercise program

o Chronic illness that makes 6-year survival improbable, or illness which requires or is likely to require treatment known to affect glucose tolerance (e.g. corticosteroid drugs)

o Mental or medical characteristics that are likely to interfere with informed consent, compliance with diet, exercise, or long-term follow-up

These eligibility and exclusion criteria are specified for the following reasons. The age range of 40-64 years is chosen to include a target population old enough for IGT to have a substantial prevalence to make screening feasible and young enough that the mortality rate will not cause many censored observations when development of diabetes is the primary endpoint. Pregnancy is to be avoided because of its effects on glucose tolerance and interference with treatment procedures. Subjects must be overweight and not participating in a vigorous exercise program, because weight loss and exercise will be components of the diet-exercise intervention. As first occurrence of diabetes will be the primary endpoint, it must not already have been diagnosed at entry. Previous treatment of IGT (such as by diet or exercise) may have established permanent changes in behavior which would make randomization to the standard diet-exercise group impractical. Entry of patients treated with drugs known to affect glucose tolerance would confuse interpretation of findings. The other medical contraindications are to avoid randomizing patients who would be unlikely to be able to maintain randomized treatment throughout the study.

Because diet is generally shared among members of a household, the enrollment of more than one person from the same household would compromise the independence of individual treatments. But since there are also benefits in enrolling both the husband and wife, they can be enrolled, but only the first one of them is randomized according to the randomization list and the spouse is assigned to the same treatment group.

The use of thiazide diuretic or beta blocker may affect glucose tolerance. Where appropriate, treatment may be changed to an ACE inhibitor or a calcium antagonist. If the subjects can not or does not want to change the medication, the subject can be eligible with the understanding that this drug treatment will not be altered without a major indication.

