3.8 SAMPLE SIZE AND ENROLLMENT GOAL

We begin sample size determination by estimating the 5-year incidence of diabetes in the untreated persons with IGT to be 28% (see Chapter 2). Because of the uncertainty in the data needed to make this estimate, this figure may be an underestimate of the incidence of diabetes. If so, the power of the study would be greater than the following computations indicate. We are designing the study to be large enough to be able to detect, with 80% power (beta = 20%) at the 2-tailed 5% significance level (alpha = 5%), a 30% reduction in diabetes incidence due to diet-exercise treatment, ie, a reduction from 28% to 19.6%.

The possibility of a reduction in diabetes incidence by at least 30% is suggested by the results of the Malmöhus study (Sartor, et al, 1980) analyzed in accordance with randomized treatment assignment and by the nonrandomized treatment study of Eriksson and Lindgärde (1991). We are assuming that noncompliance in the DPS will be no worse than in these previous studies; therefore we are making no further adjustment for noncompliance. We will, however incorporate an adjustment for losses to follow-up, including deaths.

Letting p1 and p2 denote, respectively, the proportion of events (incidence of diabetes) in the control and treated groups, respectively, then, according to Halperin, et al (1968), the sample size required in each of the two groups is

N = {Zα[2p(1 - p)]1/2 + Zß[p1(1 - p1) + p2(1 - p2)]1/2}2 / [p1 -p2]2,

where p = (p1 + p2)/2 and Zα and Zß are the normal deviates associated with α and ß. With p1 = .28, p2 = .175, α (2-tailed) = .05, and ß = .20, the total minimum required sample size becomes

2N = 500.

In Malmöhus County from 1962-87, the mortality rate among persons aged 45-64 with IGT by WHO criteria was 19/1000 persons per year (Knowler, et al, in preparation), yielding an estimated 5.5-year cumulatie mortality rate of 10% in study participants. Allowing for 10% losses to follow-up from deaths over a 5.5-year period increases the sample size to

2N = 500/(1 - .10) = 556, or approximately 560.

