8.3 OUTCOME VARIABLES

8.3.1 Events. The primary outcome variable is the incidence of diabetes. Other events of interest are defined in Chapter 7. The cumulative incidence of events, by treatment group and, to evaluate prognostic factors, by subgroups determined by pre-randomization characteristics such as those listed in Section 5.3.2, will be analyzed in 1-year follow-up intervals by the lifetable method.

8.3.2 Continuous variables. Mean changes in the following variables, by treatment group and subgroups defined by pre-randomization characteristics, will be analyzed in 1-year follow-up intervals:

o systolic and diastolic blood pressure

o waist-hip ratio; waist and hip circumference

o sagittal and transverse diameters

o body mass index

o lean body mass

o GTT

o serum cholesterol

o serum triglycerides

o serum creatinine

o plasma glucose

o plasma insulin

o serum c-peptide

o glycosylated hemoglobin

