8.4 CLINICAL COURSE AND PROGNOSIS

In addition to the comparisons of outcomes between groups according to treatment assignment, clinical course and prognosis within treatment groups will be assessed; in this regard, the group assigned to the standard diet-exercise program will be of primary interest in that this group will provide information on the natural history of IGT.

Both univariate and multivariate (eg, logistic regression and proportional hazards) analyses, with the risk factors of Section 11.4 as independent variables and the events of Section 11.3 as dependent variables, will be attempted, as will lifetable analyses (eg, Kaplan-Meier) of events.

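### Life-table cumulative incidence with deaths censored modestly overstates absolute diabetes incidence in each arm; the treatment comparison is practically unaffected

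*Protocol*

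**What the plan says.** Protocol section 8.3.1 makes the incidence of diabetes the primary outcome and says that its cumulative incidence, by treatment group and by baseline subgroup, "will be analyzed in 1-year follow-up intervals by the lifetable method". Section 8.4 describes clinical course and prognosis, with the standard arm as the main source on the natural history of IGT; regression models will be attempted, "as will lifetable analyses (eg, Kaplan-Meier) of events".

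Two other places show how deaths are viewed. Section 5.1.2 justifies the age range as "young enough that the mortality rate will not cause many censored observations when development of diabetes is the primary endpoint". Section 3.8 reports from an earlier Swedish cohort that "the mortality rate among persons aged 45-64 with IGT by WHO criteria was 19/1000 persons per year", converts this to a 5.5-year cumulative "mortality rate of 10% in study participants", and inflates the sample size for these deaths as losses to follow-up.

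Section 3.1.2 follows participants to the end of the study or death, and section 3.1.3 records death from any cause as a secondary endpoint. Death is nowhere named as a competing event for diabetes.

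**The concern.** Cumulative incidence is ordinarily read as the proportion who develop diabetes by a given time. A single-event life table with deaths censored does not estimate that proportion. It assumes that those who died would have gone on to develop diabetes at the same rate as survivors. Because death rules out later diabetes, the life-table figure lies above the proportion that can actually occur, and a larger sample does not remove the gap.

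At stake are the absolute figures: incidence by arm, to a lesser degree the absolute risk reduction, and the standard-arm natural-history estimate. A comparison of cause-specific hazards with deaths censored does not suffer from this problem.

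**Working it through.** **Inputs (protocol section 3.8 unless noted).** Control 5-year diabetes incidence 28%. Special arm 19.6% (the stated 30% reduction) or 17.5% (the value entered in the sample-size formula); both are carried because the section gives both. Mortality 19/1000 per year. Total 560 in two groups, taken as 280 per arm. Follow-up 5 or 6 years (section 3.6).

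**The protocol's own mortality figure.** 1 − exp(−0.019 × 5.5) = 9.9% (linear: 0.019 × 5.5 = 10.45%), which agrees with the stated 10%.

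**Method.** Constant hazards: diabetes λ = −ln(1 − p)/5, death μ = 0.019, equal in both arms.

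- Life table with deaths censored: 1 − exp(−λt)
- Proportion who develop diabetes, death competing: λ/(λ+μ) × [1 − exp(−(λ+μ)t)]
- Greenwood-type SE: exp(−λt) × √{λ[exp((λ+μ)t) − 1]/[(λ+μ) × 280]}

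**Control arm at 5 years.** λ = −ln(0.72)/5 = 0.0657 and λ+μ = 0.0847. The life table gives 28.0%. With death competing, 0.0657/0.0847 × [1 − exp(−0.4235)] = 26.8%. The difference is 1.22 points. The Greenwood SE is 2.75 points, so the ratio is 0.44.

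| Arm (5-year incidence) | Years | Life table % | Death competing % | Excess, points | Excess / Greenwood SE | Excess / binomial SE |
|---|---|---|---|---|---|---|
| Control (28%) | 5 | 28.00 | 26.78 | 1.22 | 0.443 | 0.454 |
| | 5.5 | 30.33 | 28.89 | 1.44 | 0.510 | 0.524 |
| | 6 | 32.58 | 30.91 | 1.67 | 0.579 | 0.597 |
| Special (19.6%) | 5 | 19.60 | 18.73 | 0.87 | 0.358 | 0.367 |
| | 5.5 | 21.33 | 20.30 | 1.03 | 0.411 | 0.423 |
| | 6 | 23.03 | 21.82 | 1.21 | 0.467 | 0.481 |
| Special (17.5%) | 5 | 17.50 | 16.72 | 0.78 | 0.335 | 0.344 |
| | 5.5 | 19.07 | 18.14 | 0.93 | 0.385 | 0.396 |
| | 6 | 20.61 | 19.52 | 1.09 | 0.437 | 0.450 |

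The relative excess is 4.6% to 5.6%. An actuarial table in 1-year intervals, as section 8.3.1 describes, gives nearly the same control-arm excess: 1.24 points at 5 years and 1.71 at 6. If only half the arm remains under follow-up after year 5, the control ratios fall to about 0.48 at 5.5 years and 0.53 at 6.

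**Between arms, equal mortality.**

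| Special arm | Years | Difference, life table | Difference, death competing | Shift, points | Shift / SE | Risk ratio, life table → competing |
|---|---|---|---|---|---|---|
| 19.6% | 5 | 8.40 | 8.05 | 0.35 | 0.098 | 0.7000 → 0.6994 |
| 19.6% | 6 | 9.55 | 9.08 | 0.46 | 0.123 | 0.7070 → 0.7061 |
| 17.5% | 5 | 10.50 | 10.06 | 0.44 | 0.125 | 0.6250 → 0.6243 |
| 17.5% | 6 | 11.96 | 11.38 | 0.58 | 0.158 | 0.6327 → 0.6318 |

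**Sensitivity to mortality (control arm, 6 years, binomial SE).** At 10/1000 per year the excess is 0.90 points (0.32 SE); at 5/1000 it is 0.45 points (0.16 SE). These two rates are assumptions; the protocol gives only 19/1000.

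**The case against.** The case against giving this much weight is substantial.

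- *The handling of deaths is inferred.* No analysis section says outright that deaths are censored; the explicit wording is in an eligibility rationale, and such detail is often left to a statistical analysis plan. This stands as a caution. But the protocol does name the quantity and fix the estimator, and a single-event life table leaves no other natural place for deaths.
- *Death-censored incidence is a legitimate quantity.* That is true for describing the natural history of IGT, but it should then be labelled as such and not presented as the proportion who develop diabetes.
- *Mortality may be lower than planned.* The 19/1000 comes from a 1962–87 cohort aged 45–64. This trial enrols from age 40, excludes illness that makes 6-year survival improbable and requires a completed walking test. The overstatement shrinks accordingly.

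Some stronger readings are tempting but not supported:

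- *That the overstatement exceeds half a standard error in general.* At 5 years, the horizon of the 28% assumption, it is about 0.45 in the control arm. It is on the boundary at 5.5 years, exceeds half only in the control arm towards 6 years, and never does so in the special arm.
- *That annual testing raises the control gap to 1.5 and 2.0 points.* That sets the life table against 26.5% at 5 years and 30.6% at 6, which count only those who survive to the next annual test. The proportions who develop diabetes are 26.8% and 30.9%; the further 0.3 points is diabetes undetected before death, not error from censoring.
- *That unequal mortality distorts the effect.* If special-arm mortality were a third lower, the 6-year difference would fall from 9.55 to 8.7 points. That contrast comes from an earlier study (section 2.3.1) whose groups section 2.2.3 says were not randomised.
- *That section 5.1.2 contradicts section 3.8.* The former is a qualitative reason for an age limit. The 10% also covers all deaths, whereas only deaths before diabetes censor the endpoint: 0.019/0.0847 × [1 − exp(−0.0847 × 5.5)] = 8.4% of control participants, about 23 of 280.
- *That the secondary events share the problem to the same degree.* This was not computed, and several of them include fatal cases.

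**Conclusion.** The concern holds for absolute incidence. Followed as written, sections 8.3.1 and 8.4 would report diabetes incidence about 5% too high in relative terms: 1.2 to 1.7 points in the control arm (about 0.44 to 0.6 SE) and 0.8 to 1.2 points in the special arm (about 0.34 to 0.48 SE) at 5 to 6 years. This rests on constant hazards, equal mortality of 19/1000 per year, 280 per arm, and reading deaths as censored from sections 5.1.2 and 3.8. Taking the 28% as incidence with deaths already present changes little: the control ratios become 0.47, 0.54 and 0.61 (binomial SE) at 5, 5.5 and 6 years.

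A reader might infer that the efficacy conclusion is at risk. It is not: with equal mortality the arm difference moves by 0.10 to 0.16 SE, the risk ratio by less than 0.001, and the cause-specific comparison with deaths censored remains valid. The point is a modest one of matching the estimator to the quantity named.

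**What to change.** In section 8.3.1, and in the standard-arm natural-history description in section 8.4, estimate and report the absolute cumulative incidence of diabetes with death before diabetes as a competing event (Aalen-Johansen). Keep the life-table or Cox comparison with deaths censored, and label it as the cause-specific treatment comparison.

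The age-range rationale in section 5.1.2 needs no correction. The change requires no additional participants or data, since deaths are already recorded as a secondary endpoint. The cost is a few sentences of analysis text, a little more analysis, and reported incidences lower by roughly 1 to 1.7 points if mortality is as planned.

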3.1 STUDY PURPOSE AND DESIGN SUMMARY

3.1.1 Purposes. The Diabetes Prevention Study (DPS) has three major purposes:

1) to assess the efficacy of a special diet-exercise program in preventing or delaying the onset of type 2 diabetes in persons with IGT, and

2) to study the risk factors for progression to diabetes in persons with IGT.

3) to assess the effects of the intervention on atherosclerotic vascular disease.

3.1.2 Primary Endpoint. The primary endpoint is diabetes, as defined in detail in Chapter 7.

Subjects will remain in the study and be followed until the end of the study or death, whichever occurs earlier. Study treatments will be continued until the end of the study, death, or the occurrence of diabetes, whichever occurs earlier.

3.1.3. Secondary endpoints. Subjects will also be monitored for the following secondary endpoints as defined in detail in Chapter 7:

1) Fatal or non-fatal myocardial infarction or sudden cardiac death.

2) Angina pectoris.

3) Intermittent claudication.

4) Stroke.

5) Death from any cause.

3.1.4 Subjects. Subjects with IGT will be found by population screening. A total of 560 subjects at several Clinical Centers will be treated and followed for at least five years. Each subject will be randomly allocated to a special or standard diet-exercise program. A Central Laboratory will make biochemical measurements, and a Coordinating Center will coordinate study activities and provide central data management and statistical support.

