3.5 REGISTRATION, RANDOMIZATION, AND STRATIFICATION

3.5.1 Treatment assignment and registration. Assignment will be issued by the Clinical Center which will register enrollment of subjects upon verification that all eligibility criteria have been met.

3.5.2 Randomization to treatment. Subjects will be randomly allocated to special or standard diet-exercise program in the following way:

Group 1: Special diet - exercise

Group 2: Standard diet - exercise

3.5.3 Stratification. Randomization will be stratified by 1) Clinical Center and 2) the 2-hour post-load glucose obtained during the OGTT:

o Stratum 1: venous plasma glucose = 7.8-9.4 mM (140-169 mg/dl)

o Stratum 2: venous plasma glucose = 9.5-11.0 mM (170-199 mg/dl)

3.5.4 Registration. Subjects are enrolled in the DPS as soon as they are registered by the Clinical Center. The Clinical Center will promptly register a subject upon verification that all eligibility criteria have been met. A registration number (and treatment assignment) is given to the subject according to the randomization list.

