3.7 MASKING

3.7.1 The diet-exercise intervention will be only partly masked. This assignment can obviously not be masked from the subjects or from those Clinical Center personnel who counsel the subjects on their diet or exercise programs. However, all laboratory personnel, including those performing the glucose tolerance test, and the Endpoints Committee (Chapter 8) will be masked.

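### A second spouse takes the partner's arm without randomization, and nothing requires the spouse to be eligible and consented before that arm is known

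*Protocol*

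**What the plan says.** The household paragraph at the end of section 5.1.2 first states the difficulty: "the enrollment of more than one person from the same household would compromise the independence of individual treatments". It then makes an exception: "since there are also benefits in enrolling both the husband and wife, they can be enrolled", with the rule that "only the first one of them is randomized according to the randomization list and the spouse is assigned to the same treatment group". It sets no limit on the number of couples and does not say when the second spouse must be screened and consented relative to the partner's allocation.

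Other sections describe allocation with no such exception:

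- Section 3.1.4: "Each subject will be randomly allocated to a special or standard diet-exercise program".
- Section 3.5.3: "Randomization will be stratified by 1) Clinical Center and 2) the 2-hour post-load glucose obtained during the OGTT". Section 3.5 does not mention spouses.
- Section 3.7.1, on masking: "This assignment can obviously not be masked from the subjects or from those Clinical Center personnel who counsel the subjects".

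The sample size in section 3.8 comes from a formula for two independent proportions. For the analysis, section 8.3.1 says that the cumulative incidence of events "will be analyzed in 1-year follow-up intervals by the lifetable method". Section 8.4 adds logistic regression, proportional hazards and Kaplan-Meier methods. None of these is described with a household term.

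**The concern.** Two separate things are at stake.

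The first is allocation. A second spouse has no draw of his or her own. If the couple enters together, before the draw, this does no harm, because the couple is simply allocated as a unit. If the spouse can enter after the partner has been allocated, the spouse and the staff may both know the arm when the spouse decides whether to join. Some of the protocol's own features make that knowledge relevant. Section 3.8 allows the prospect of an intervention programme to be used to encourage recruitment. The two programmes in section 6.1 differ greatly in contact and support. The exclusions in section 5.1.2 include a judgement about likely compliance, which staff could be making with the arm known. Enrolment of second spouses could then differ between arms in number and in type of person. A later choice of analysis model cannot fully undo that.

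The second is precision. Spouses share a household diet, as section 5.1.2 itself says, and both are always in the same arm. Any positive correlation between their outcomes makes the usual standard error too small.

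**Working it through.** **Setting the sections side by side.** Section 3.1.4 says each subject is randomly allocated; section 5.1.2 says a second spouse is not. Both cannot stand. Section 3.5 describes the randomization list and strata without saying how a second spouse is registered. Section 5.1.2 speaks of the first spouse being randomized but does not say whether the other must already be eligible and consented. Section 3.7.1 confirms that the arm is open to subjects and counsellors. Late entry with knowledge of the arm is therefore permitted, although it is not prescribed.

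**The plan's own sample size.** Inputs from section 3.8: p1 = 0.28, p2 = 0.175, two-sided alpha 0.05 (z = 1.960), power 80% (z = 0.842), equal groups.

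- Mean p = (0.28 + 0.175)/2 = 0.2275.
- First term: 1.960 × √(2 × 0.2275 × 0.7725) = 1.162.
- Second term: 0.842 × √(0.28 × 0.72 + 0.175 × 0.825) = 0.495.
- N = (1.162 + 0.495)² / 0.105² ≈ 249, taken up to 250 per group, so 2N = 500.
- With 10% losses: 500/0.90 = 556, rounded in the plan to 560.

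The stated figures reproduce exactly with no clustering term, so the calculation leaves nothing for couples. The rounding to 560 covers only a design effect of 560 × 0.90/500 = 1.008. (The 17.5% used here is not the 19.6% that the same section names as its target. That is a separate and much larger matter, and 17.5% is kept here only to follow the plan's figure.)

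**Effect of couples on precision.** Let s be the share of subjects enrolled as couples and ICC the within-couple correlation. With clusters of two, both in one arm, the design effect is DE = 1 + s × ICC, and the true standard error is √DE times the naive one. The protocol gives neither s nor ICC. The assumed ranges are s = 10-20% and ICC = 0.1-0.5. Of 560 subjects, 10-20% is 56-112 people, or 28-56 second spouses.

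| s | ICC | DE | SE ratio | 2N needed | after 10% loss | actual alpha | power at 250 per arm |
|---|---|---|---|---|---|---|---|
| 10% | 0.1 | 1.01 | 1.005 | 505 | 562 | 0.051 | 79.8% |
| 10% | 0.2 | 1.02 | 1.010 | 510 | 567 | 0.052 | 79.4% |
| 10% | 0.5 | 1.05 | 1.025 | 525 | 584 | 0.056 | 78.2% |
| 20% | 0.1 | 1.02 | 1.010 | 510 | 567 | 0.052 | 79.4% |
| 20% | 0.2 | 1.04 | 1.020 | 520 | 578 | 0.055 | 78.6% |
| 20% | 0.5 | 1.10 | 1.049 | 550 | 612 | 0.062 | 76.3% |

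Actual alpha is 2 × [1 − Φ(1.960/√DE)] when the naive standard error is used. Power uses 250/DE per arm, against 80.15% with no couples.

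**Selection.** If second spouses make up a share f of each arm and their underlying risk differs by d between arms for reasons of selection, the bias in the risk difference is f × d. The protocol gives no value for f or d and no sign for d. For scale only: s = 10-20% means f = 5-10%. With d assumed at 5-10 percentage points, the bias is between 0.05 × 5 = 0.25 and 0.10 × 10 = 1.0 percentage point. At 250 per arm and 28% risk, the standard error is √(2 × 0.28 × 0.72/250) = 0.040, and the false-positive rate moves from 0.050 to between 0.050 and 0.057.

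**The case against.** Keeping a couple in one arm is a reasoned choice. Household diet is shared, and splitting couples would contaminate the comparison. The wording also fits spouses who are screened and enrolled together, in which case the selection route largely closes. A second spouse must personally meet the glucose, body mass index and age criteria, so couples may be few. Laboratory staff and the Endpoints Committee are masked, which protects outcome ascertainment. Variance estimation and analysis sets are normally left to a statistical analysis plan, and one that is not shown here could already cluster on household.

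Most of this stands, and it limits the point. It does not answer the contradiction with section 3.1.4 or the missing rule on the order of consent and allocation. Both are protocol matters, and a clustered variance would not cure non-random entry.

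A reader might go further in four ways that the document does not support:

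- That second spouses do enter already knowing the arm. The text allows this but does not say so.
- That the bias favours the special programme. A higher-risk spouse might be just as keen to join it, so the sign is open. Unequal numbers of spouses alone would bias nothing without a difference in risk.
- That the analysis will treat spouses as independent. This is explicit only in the sample-size formula. For the analysis it is an inference from the methods named.
- That missing a draw within the spouse's own glucose stratum is a further fault. Any couple-level allocation has that feature, and section 8.2 already provides for covariate adjustment if baseline balance fails.

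**Conclusion.** The point holds as a gap in the allocation rule plus an unallowed-for correlation, of minor to moderate weight. Section 5.1.2 contradicts section 3.1.4, has no counterpart in section 3.5, and leaves open the entry of non-randomized subjects who know their arm. Selection bias in the primary comparison is possible, but its size and direction cannot be derived from the protocol; the fractions of a point shown above are illustrations under assumed inputs. The loss of precision is small. The standard error is about 1% larger than the naive one at 10% in couples and ICC 0.2, and about 5% larger at 20% and ICC 0.5. Both inputs are assumptions, and an unseen analysis plan may already deal with the variance. The document does not support a claim that the trial's result would be materially distorted. The reason to act is that the order of entry cannot be repaired after enrolment, while fixing it beforehand costs almost nothing.

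**What to change.** 1. In section 5.1.2, make the couple the unit of allocation: both spouses are screened, found eligible and consented before a single draw is made for the couple.
2. Keep any spouse who enters after the partner's allocation out of the primary analysis. Such a spouse may be followed and included in a sensitivity analysis.
3. State in Chapter 8, or in the analysis plan, that the variance for the primary comparison is clustered on household, and report the number of couples by arm.
4. Reconcile sections 3.1.4, 3.5 and 5.1.2, so that the general allocation statement names the couple exception and section 3.5.3 says which spouse's glucose value sets the stratum for the draw.

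The cost is a few sentences. A few late spouses would leave the primary analysis set, and precision would fall slightly.
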